**Fig. 1 Fig1:**
[figure not shown]
CONSORT diagram of recruitment and participation for people with aphasia

**Fig. 2 Fig2:**
[figure not shown]
CONSORT diagram of recruitment and participation for peer befrienders

### Blinding

The chief investigator, study statisticians, and research assistants collecting post-baseline quantitative data will be blinded to treatment allocation until data collection is complete. To ensure blinding of quantitative outcome measures, research assistants will not have access to participant details, they will follow a script when completing visits, all visits will be arranged by the Trial Manager, and participants will be asked to not reveal information regarding interventions they have received during assessment. If a research assistant becomes unblinded, they will report this to the Trial Manager who will keep a record of such instances. If this happens during the 4-month assessment point, the 10-month assessments will be completed by another research assistant. Statisticians will receive treatment group with partially blind coding (i.e. A and B), and data that would unblind will be stored in a separate database that will not be accessed by the trial statisticians until the main primary analysis is done. The Trial Manager, qualitative researchers, health economics researchers, and the befriender supervisor will be unblinded.

### Intervention

#### Intervention arm—usual care + peer befriending (PEER)

Participants in the intervention arm will receive all usual care available in their borough and peer befriending. Peer befriending aims to utilise the skills, knowledge, and ‘lived experience’ of people with longer-term aphasia to offer emotional, social, and informational support to others with aphasia. It aims to help people move forward and develop their own strategies for adjusting to life post-stroke. In the trial, peer befriending is offered at a time of transition (discharge from hospital and withdrawal of intensive therapeutic input) and increased need. The intervention is described according to the TIDieR checklist [28] (see Additional files 2).

Peer-befrienders will receive training based on a study-adapted version of a peer befriending intervention manual [42] and ongoing supervision and support. The training will last 5–6 h across 2–3 days to accommodate the needs of the participants in the group (e.g. levels of attention and fatigue). The training will be conducted by two facilitators, who both have experience of communicating with people with aphasia. One of the trainers has additional experience of running peer befriending schemes. The training will cover a range of topics related to peer befriending (e.g. the role of a befriender, hopes and fears, how to have a conversation as a befriender, setting objectives, identifying barriers, dealing with challenging situations), health and safety, and dealing with adverse events. Peer befrienders will receive a copy of a peer befriender handbook, which contains key information from the manual in aphasia-accessible format. It is anticipated that each peer-befriender will work with 2–4 participants during the trial and no more than two at any one time.

Peer-befrienders will be offered monthly group supervision sessions. These sessions will be conducted by a single befriender facilitator (also involved in the training) who is a trained SLT with extensive experience in working with people with aphasia. The sessions will be an opportunity to share experiences and discuss any difficulties that have arisen. Peer-befrienders who are facing particular challenges will receive supplementary individual supervision and support from the same befriender facilitator. Peer befrienders and the facilitator will record these challenges. The facilitator will keep detailed written notes to summarise the content of each supervision session.

Trained peer-befrienders will visit participants in their own home six times (each visit aimed to be at least 1 h) over a period of 3 months. A further two visits within the next 6 months will also be offered for a gradual transition to the end of the peer befriending. Participants will be paired with and introduced to their peer-befriender as soon as possible after and within 1 month of randomisation. If this is not feasible, the reasons for this will be recorded. Where possible, pairing will take account of preferences around gender, cultural factors, age, and personal interests. The schedule and nature of visits will be agreed between the pair at their first meeting. This meeting will also identify possible goals for the intervention. For example, participants might highlight concerns that they would like to discuss or activities that they would like to pursue. Subsequent visits may include conversation, problem-solving, trips out e.g. to a local group, and joint activities.

After each visit peer-befrienders will complete an aphasia-friendly record sheet. This will include whether a visit was cancelled and reason why, length of visit, topics discussed, activities undertaken, any decisions made, and date and time of next visit. Peer befrienders will complete this record sheet immediately or as soon as possible after each visit if necessary with the help of the befriender facilitator who will collate these sheets during monthly supervision sessions. The facilitator will pass the record sheets on to the Trial Manager on a monthly basis.

#### Control arm—usual care (USUAL)

The control group will receive usual care, comprising of all the health care, social care, and voluntary services available in their borough. It is not known what exactly usual care comprises for people with aphasia who are discharged in the community with low levels of psychological problems. This trial will help to document usual care by administration of the CSRI questionnaire.

#### Intervention fidelity

The fidelity of the peer befriender training and supervision and the peer-befriending intervention will be evaluated. Fidelity checklists have been created for each of these three session types to measure how closely they adhere to the peer befriending intervention manual, the handbook, and the intended aims of the intervention. These checklists have been informed by the Health Behaviour Change Competency Framework (HBCC) [43] and rating scales of the interactions of people with aphasia and their communication partners [44].

All training and supervision sessions will be videotaped. All training sessions and all supervision sessions, except the first and the last, will be watched by unblinded team researchers and research students and rated against the fidelity checklists to ensure training and supervision are delivered as intended. With participants’ consent, a proportion of befriending visits (1 per participant) will also be videotaped and watched against a fidelity checklist. Results from these checks will be reported back to the befriender facilitator to inform later content of the supervision sessions.

Information from the supervision notes and from the peer befriender visit record forms will also be used to evaluate whether peer befrienders followed the peer befriending handbook and to compare content of intervention between and within different peer befrienders. This information will provide additional qualitative information and context on the fidelity of the intervention.

### Procedures

Outcome measures data will be collected by blinded research assistants/assessors who are trained and skilled in communicating with people with aphasia. Assessors will be given a data collection pack for each participant, at each time point. These packs will contain a script to guide their conversations with participants and verbal instructions for each of the outcomes administered. During the development phase of the trial, an example assessment session was videotaped between a member of the research team and a person with aphasia (consultant with aphasia, see User and public involvement). This training video will be used to ensure consistent administration of the outcome measures. In addition, the Trial Manager will observe the first videotaped assessment session of each assessor. Further assessment sessions will be observed at random by the Trial Manager either in person or by reviewing videotaped sessions.

The qualitative research assistant conducting the semi-structured interviews will similarly be supported. They will receive training in conducting semi-structured interviews from a senior qualitative researcher in the team, who has extensive experience of adapting qualitative methodologies for people with aphasia. The senior qualitative researcher will listen to two audiotaped initial interviews and give feedback, for example, to ensure questioning is unbiased and leads to the full exploration of topics. They will continue to support the qualitative research assistant throughout the trial and will periodically listen to interviews.

For the economic evaluation, either the Trial Manager or the qualitative research assistant will collect information using a stroke adapted version of the Client Service Receipt Inventory (CSRI) [45]. They will be given training in completion of the CSRI and eliciting resource use information by a member of the study team with relevant health economics expertise. As much information as possible will be collected from the significant other as primary respondent, where available. The Trial Manager will draw additional information by contacting CRN nurses or members of the clinical team as appropriate.

To facilitate participants to attend baseline and follow-up sessions, participants, significant others and peer befrienders will be contacted by text/telephone at least 1 week prior to each assessment session and on the previous day to confirm appointment times. To maximise retention and participant engagement in the project, a quarterly newsletter will be sent out, and a single phone-call between follow-up assessment times will also be made to remind them of their next appointment.

### Measures

At baseline, all participants will complete a case history covering: demographic and health information, family and social circumstances, and personal interests. This information will be used to report on participant characteristics and will also contribute to pairing with peer befrienders for those in the intervention arm. For participants with aphasia, aphasia will be fully assessed with the Western Aphasia Battery-Revised [46], and cognition with the Cognitive-Linguistic Quick Test (CLQT) [47], which has been specifically developed for people with aphasia. These assessments will be reported descriptively under participant characteristics.

#### Feasibility outcomes

Feasibility outcomes will include the following:

Proportion of participants with aphasia who are eligible of those screenedProportion eligible at first screenProportion eligible at second screenThe rate of eligibility per monthProportion who consent of those eligibleThe rate of consent per monthThe rate of recruitment (participants randomised) per monthThe frequency and proportion of people consented who withdraw overall, by study arm, and by those who do before and after randomisation. This will specifically include describing those in the PEER arm who decline consent at the second stageAcceptability of research procedures and outcome measures based on qualitative interviewsAcceptability of the intervention and also usual care to participants, their significant others, and peer befrienders, based on qualitative interviewsDocumentation of usual care, based on data from CSRIFidelity and adherence, based on session observations, visit record sheets, and supervision records.

Moreover, we will informally ask CRN nurses and other members of the clinical teams involved with SUPERB in all our sites about their experiences with the trial. This information will provide additional context to our feasibility outcomes.

#### Patient-reported outcome measures

A range of outcome measures will be used with participants with aphasia covering mood, wellbeing, activities, and communication and social participation. Measures chosen have either been developed specifically for neurologically impaired populations, some including people with aphasia or have been previously used with people with aphasia with good evidence of accessibility and acceptability. Where appropriate, the presentation of measures will be modified to make them aphasia-friendly in line with best practice guidelines [48]. The content, however, will not be changed to avoid affecting measures’ psychometric properties.

The following primary outcomes for participants with aphasia will be completed at baseline, 4 and 10 months post-randomisation: General Health Questionnaire-12 (GHQ-12) [32], using 0 0 1 1 scoring and the Depression Intensity Scale Circles (DISCS) [30]. The DISCS is being measured because some participants may not be able to complete the GHQ-12. This feasibility study will assess how often this is the case. The DISCS will be treated as the primary outcome measure only if there is ≥ 10% missing data in the GHQ-12 due to severity of aphasia; otherwise, DISCS will be a secondary outcome measure.

The following secondary outcomes for participants with aphasia will be taken at the same time points: Short Warwick Edinburgh Mental Well-being Scale-7 [49], Communicative Participation Item Bank [50], Community Integration Questionnaire—Adapted [51]. Proportion with high emotional distress vs low emotional distress as measured using the GHQ-12 (high distress = score of 3 or more, low distress = score of 0–2). There are additional psychological constructs that may be affected by peer befriending; however, the evidence base is not strong on whether existing measures on these constructs are responsive to change when used with people with aphasia. We will include two exploratory self-report outcomes for participants with aphasia in this study, the Communication Confidence Rating Scale for people with aphasia [52, 53] and the Friendship Scale [54] in order to see whether they may be suitable to use as secondary outcome measures in a definitive trial. These will be completed by participants with aphasia at each of the three time points.

The following outcomes for significant others will be taken at baseline, 4 and 10 months post-randomisation: Warwick Edinburgh Mental Well-being Scale [55]; General Health Questionnaire-28 (GHQ-28) [32], with 0 0 1 1 scoring and descriptive information on its four subscale scores; and Bakas Caregiving Outcome Scale [56].

Outcomes for peer befrienders will be taken at baseline and on completion of two befriending cycles, i.e. six befriending visits with each of two participants. For befrienders who do not fully complete a cycle because, e.g. the participant with aphasia dies or withdraws, the cycle will be considered completed if they have done a minimum of two visits. Outcomes comprise the Warwick Edinburgh Mental Well-being Scale-7; Community Integration Questionnaire—Adapted; and General Self-Efficacy Scale [57].

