**Methods/design:**

SUPERB is a single blind, parallel group feasibility trial of peer befriending for people with aphasia post-stroke and low levels of psychological distress. The trial includes a nested qualitative study and pilot economic evaluation and it compares usual care (*n* = 30) with usual care + peer befriending (*n* = 30). Feasibility outcomes include proportion screened who meet criteria, proportion who consent, rate of consent, number of missing/incomplete data on outcome measures, attrition rate at follow-up, potential value of conducting main trial using value of information analysis (economic evaluation), description of usual care, and treatment fidelity of peer befriending. Assessments and outcome measures (mood, wellbeing, communication, and social participation) for participants and significant others will be administered at baseline, with outcome measures re-administered at 4 and 10 months post-randomisation. Peer befrienders will complete outcome measures before training and after they have completed two cycles of befriending. The qualitative study will use semi-structured interviews of purposively sampled participants (*n* = 20) and significant others (*n* = 10) from both arms of the trial, and all peer befrienders to explore the acceptability of procedures and experiences of care. The pilot economic evaluation will utilise the European Quality of life measure (EQ-5D-5 L) and a stroke-adapted version of the Client Service Receipt Inventory (CSRI).

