#### Qualitative outcomes

Interviews will be conducted with ten participants with aphasia in each arm of the trial at 4 months post-randomisation. These interviews will explore participants’ experience of taking part in the study and also what has helped participants in adjusting to living with stroke and aphasia. They will probe what participants have found useful in terms of emotional well-being, confidence, and thoughts about the future. The interviews will also explore participant experiences of services they have received in terms of their psychological well-being post stroke. Those who received peer befriending will also be asked about their experiences of the intervention, its perceived benefits, and any difficulties. The subset of participants interviewed from the PEER arm of the trial will be re-interviewed at 10 months about the longer term impact of the stroke and aphasia and their perceptions about the intervention.

A sub-sample of five significant others from each arm will be interviewed at 4 months to explore the impact of the stroke and aphasia on their life and family life and their perspectives of the care received. Those in the PEER arm will also be asked about the administration and impact of peer befriending. All interviewed participants will be selected purposively to capture a diversity of views. Key sampling criteria for participants with aphasia are severity of aphasia and whether the person lives alone. Secondary criteria are geographical area, gender, mobility, GHQ-12 score, and ethnicity. For significant others, sampling criteria include relationship to person with aphasia (partner/spouse or child/other), ethnicity, gender, and GHQ-28 scores.

All befrienders will be interviewed after they have completed two cycles of befriending (minimum two visits per cycle) to explore their experience of the study, including reflections on programme training and delivery, support received, any concerns or difficulties, and perceived benefits of peer befriending.

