### Statistical methods: data analysis

#### Feasibility outcomes

As SUPERB is a feasibility trial, the feasibility outcomes are the most important/will take precedence. We will calculate proportion who are eligible of those screened (number eligible/number screened), proportion who are eligible at first screen (number eligible/number screened at first screen) and second screen (number eligible/number screened at second screen), rate of eligibility per month, proportion who consent of those eligible (number who consent/number eligible), rate of consent per month, and rate of recruitment (participants randomised) per month. The frequency and proportion of people consented who withdraw overall, by study arm, and by those who do before and after randomisation will be presented. This will specifically include describing those in the PEER arm who decline consent at the second stage. Appropriate 95% confidence intervals will be constructed for all of the above measures.

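### Befrienders are followed up only after two qualifying cycles, so those who leave earlier or are matched too seldom give no interview and no second score

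*Protocol article*

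**What the plan says.** The Abstract (Methods/design) gives two time points for the befriender measures: "Peer befrienders will complete outcome measures before training and after they have completed two cycles of befriending". Patient-reported outcome measures repeats this: "Outcomes for peer befrienders will be taken at baseline and on completion of two befriending cycles". It defines a cycle as six visits with one participant, and adds that when a cycle is cut short, for example by a participant's death or withdrawal, "the cycle will be considered completed if they have done a minimum of two visits".

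The interview has the same trigger. The Abstract includes "all peer befrienders to explore the acceptability of procedures and experiences of care", and Qualitative outcomes says "All befrienders will be interviewed after they have completed two cycles of befriending (minimum two visits per cycle").

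The Feasibility outcomes list under Measures includes acceptability of the intervention "and also usual care to participants, their significant others, and peer befrienders, based on qualitative" interviews. The Feasibility outcomes part of the statistical methods says that "the feasibility outcomes are the most important/will take precedence". On supply of matches, the Intervention arm section anticipates that "each peer-befriender will work with 2–4 participants during the trial". The article gives no exit interview, calendar date or end-of-befriending time point for a befriender who does not reach two cycles.

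**The concern.** Follow-up of befrienders depends on completing the role, while the question put to them is whether the role is acceptable. Those who stop early may see the role, the training or the support differently, and the rule leaves them out.

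There are two routes to being missed:

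- **Leaving or being withdrawn.** Anticipated risks and benefits foresees that a befriender in the high-distress range of the GHQ-12 may need to be withdrawn.
- **Too few matches.** This need not be the befriender's choice. The lower end of the anticipated 2–4 participants equals the threshold of two. A befriender with two matches has no spare if one participant refuses befriending at the second-stage consent, or stops before two visits.

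Participants with aphasia are handled differently. They are measured at fixed months after randomisation, however many visits they had, and are analysed first by intention to treat.

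**Working it through.** The article gives no figure on this point. Its only power statement concerns the PEER versus USUAL comparison and plays no part here. The sizes below are derived or assumed, as marked.

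**1. What the rule requires.** The relaxation lowers the visits needed per cycle from six to two, so the minimum falls from 12 visits to 4. The number of cycles stays at two. A befriender with one match, or whose second pairing ended after no visit or one, does not qualify. The aim of interviewing all befrienders is therefore met only if every befriender reaches two qualifying cycles.

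**2. Number of befrienders (derived).** With 30 in the PEER arm (Sample size) and 2–4 participants each, the number lies between 30/4 = 7.5, about 8, and 30/2 = 15.

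**3. Share lost per leaver.**

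| Leavers | of 15 | of 8 |
|---|---|---|
| 1 | 6.7% | 12.5% |
| 2 | 13.3% | 25% |

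**4. Too few matches.** Let k be the number of pairings lost before two visits. With 15 befrienders at two matches each, the best case (full re-matching) is that floor((30 − k)/2) reach two cycles. In the worst case each loss falls on a different befriender.

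| k | Short, best case | Short, worst case | Share of 15 |
|---|---|---|---|
| 1 | 15 − 14 = 1 | 1 | 7% |
| 3 | 15 − 13 = 2 | 3 | 13–20% |
| 5 | 15 − 12 = 3 | 5 | 20–33% |

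The value k = 5 borrows the Sample size allowance for loss to follow-up (60 to 50, or five per arm). It is an upper assumption, because many of those losses would come after two visits. With 8 befrienders (six with four matches, two with three), k = 5 leaves 0 to 2 short; the 2 arise if each befriender with three matches loses two.

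**5. The same question by probability.** Let q be the assumed chance that a match yields a qualifying cycle. The share falling short is 1 − q² at two matches each, and 1 − [q³ + 3q²(1 − q)] at three.

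| q | 15 befrienders, 2 matches | 10 befrienders, 3 matches |
|---|---|---|
| 0.95 | 10% | 1% |
| 0.90 | 19% | 3% |
| 0.80 | 36% | 10% |

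Loss from too few matches is therefore mainly a problem at the low end of the matching range. At three or more matches each it is small unless q is poor, but early leavers are still missed.

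**6. Effect on the paired t-test.** The shift in mean change is the share missing times the difference between leavers and the rest. Assuming a difference of 0.5 to 1 SD of change, it runs from 1/15 × 0.5 = 0.03 SD to 2/8 × 1 = 0.25 SD. The standard error of a mean change is 1/√n, which is 0.26 SD for n = 15 and 0.35 SD for n = 8. The shift stays below the standard error.

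**The case against.** The strongest reply is that the text sets timing, not eligibility. It says all befrienders will be interviewed, names when, and nowhere says that an early leaver is not. The article is also a condensed account: the full protocol (Additional file 3) and the befriender flow diagram (Fig. 2) are not shown and could contain an exit procedure. The authors foresaw incomplete cycles and lowered the bar to two visits. Monthly supervision, individual support, recorded challenges and visit sheets capture something of those who struggle. The larger percentages need the bottom of the matching range and several lost pairings. A common minimum exposure before interview is a defensible choice.

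Part of this stands. The number affected is unknown and may be nil, the larger shares are scenarios, and the supervision and visit records do give partial information.

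The rest does not remove the point. The article states the trigger three times and adds a rule for shortened cycles, so this is a stated rule that is incomplete rather than an omitted detail. If two cycles is when the interview takes place, a person who never gets there has no interview date. Intervention fidelity and the feasibility list assign the supervision notes and visit records to fidelity and adherence, and the feasibility list bases acceptability on the interviews. If the full protocol has an exit procedure, the article's wording should be brought into line with it.

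**Conclusion.** The concern holds. Followed as written, the plan obtains befriender acceptability only from those who stayed and were matched often enough, against its own aim of interviewing all. That selects the respondents for an outcome in the set the plan puts first.

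The group is about 8–15 people, so each person missed is 7–13% of it. How many would be missed depends on leaving rates and lost pairings that the article does not give. The scenarios run from none short (8 befrienders with few lost pairings) to a third short (15 befrienders, five lost pairings, all on different people). The harm is to the interview evidence; the exploratory score comparison is unlikely to be moved by more than its standard error. The change should be made, but the point does not threaten the trial as a whole.

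**What to change.** Amend one sentence in Patient-reported outcome measures and its counterpart in Qualitative outcomes: offer the befriender interview and the follow-up measures at two qualifying cycles, on leaving the role, or at the end of befriending, whichever comes first. Report all befrienders who started, with the visits each completed, and show those who completed two cycles separately. Give the number who decline, with reasons.

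Where befriending has already ended, leavers can still be approached, and the number not interviewed should be reported.

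The cost is a few extra interviews and questionnaires among about 8–15 people. Exposure will vary among those seen at exit, which is why completers should be shown separately. Some leavers, especially those withdrawn from the study, will decline.
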